**13.3.4. Safety Analysis**

Safety assessment is performed based on all adverse reactions, vital signs, blood tests, etc. collected from the subject.

All the above safety variable data collected up to 3 months after the procedure are presented for each time point at which each safety endpoint was measured and for each subject, and summary statistics are presented. Adverse events collected from subjects will be coded using MedDRA. Adverse events, adverse medical device reactions, SAEs, deaths, adverse events that resulted in clinical trial discontinuation, and the number of subjects who exhibited each adverse reaction will be summarized by the system organ class (SOC), preferred term (PT) and maximum severity.

1. **Clinical Trial Discontinuation and Dropout Criteria**

If participation is withdrawn after consent to participate in the clinical trial, or if participation in the clinical trial is judged to affect the safety of the subject under the judgment of the principal investigator, participation in the clinical trial may be suspended or the subject may be withdrawn from participation.

ALPINION Medical Systems Co., Ltd. 32/45

Protocol No. APM-03 Version 1.10/Date 20180103

**14.1. Discontinuation Criteria**

① If the circumstances observed during the clinical trial make it unreasonable to proceed with the clinical trial, the clinical principal investigator may suspend the clinical trial, must immediately notify the Institutional Review Board of this fact and submit a statement of reason for early termination or suspension.

② The clinical trial may be stopped in the event of a life-threatening serious adverse reaction/adverse medical device or to treat the adverse reaction that has occurred.

**14.2. Dropout Criteria**

① When the subject or legal representative requests to stop participating in the clinical trial

② In case of concomitant use of surgery, drug, or medical device that may affect safety and efficacy assessment

③ In case a serious adverse reaction occurs and it is impossible to continue participation in the clinical trial

④ If treatment is not performed properly

⑤ If the subject does not comply with the instructions of the investigator or does not comply with the matters presented in the consent form, which affects the assessment of efficacy

⑥ In case the subject dies due to reasons not related to the clinical trial

⑦ If the clinical trial manager determines that there is a problem with the clinical trial

**14.3. Handling Discontinuations**

① If the clinical trial is suspended, the reason for the suspension and the data related to the clinical trial conducted before the suspension are recorded and stored, and a statement of reason is submitted.

② Appropriate measures and follow-up should be made when the clinical trial is discontinued.

③ All discontinued subjects will be included in the safety analysis and will be excluded from the efficacy assessment.

**14.4. Handling Dropouts**

① In case of dropping out of a clinical trial, record and keep the reasons for withdrawal and data related to the clinical trial conducted before dropping out, and submit a statement of reason to the Institutional Review Board.

② All data collected until the subject's dropout will be included in the safety analysis and will be excluded from the efficacy assessment.

1. **Assessment Criteria, Assessment Method and Reporting of Safety Including Side Effects**

ALPINION Medical Systems Co., Ltd. 33/45

Protocol No. APM-03 Version 1.10/Date 20180103

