**11.6.3. Concomitant Therapy**

Drugs that may affect the treatment of adenomyosis (see Contraindicated Drugs below) or alternative treatments are prohibited. All drugs already being taken due to underlying diseases are recorded at the time of Screening. Only the drugs added thereafter are recorded in the CRF. If any of the above contraindicated drugs or alternative treatments were received during the clinical trial period, they will be withdrawn from the study and the reason for withdrawal should be recorded.

However, even if it is a contraindicated drug, if a one-time administration is necessary regardless of this study, it can be used within the extent that does not affect the procedure result at the discretion of the investigator and the related information is recorded in the concomitant drugs section of the CRF.

Subjects are administered midazolam and fentanyl for sedation prior to the procedure. The dosage of midazolam and fentanyl is determined by the investigator in consideration of the age and clinical condition of the subject, but generally midazolam 3mg/3ml or 5mg/5ml, and fentanyl 100mcg/2ml are administered. At the discretion of the investigator, analgesics, sedatives and local anesthetics may be administered according to the standard procedure of the institution in consideration of the subject's condition.

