**16.6. Care and Treatment Criteria of Subjects After Clinical Trial**

If the subject drops out of the clinical trial due to an adverse event or if there are side effects and residual symptoms due to the adverse event even after the completion of the clinical trial, the subject will receive adequate treatment until recovery by taking appropriate medical measures according to the standard medical guidelines of the hospital. Subjects who have completed the clinical trial without adverse events will be subject to general clinical observation according to standard hospital procedures after the clinical trial.

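### Section 14.4 takes a dropout's safety data only up to dropout, and nothing provides adverse event follow-up to Month 3 afterwards, so the 3-month adverse event rates could be biased low

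*Protocol*

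**What the plan says.** **What happens to the data.** Section 14.4 of the protocol has two items. The first tells the site to "record and keep the reasons for withdrawal and data related to the clinical trial conducted before dropping out". The second says "All data collected until the subject's dropout will be included in the safety analysis" and, in the same sentence, takes those data out of the efficacy assessment.

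**Who leaves.** Section 14.2 lists the dropout criteria. Three matter here:
- "In case of concomitant use of surgery, drug, or medical device that may affect safety and efficacy assessment"
- "In case a serious adverse reaction occurs and it is impossible to continue participation in the clinical trial"
- "If treatment is not performed properly"

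Section 11.6.3 adds that women who receive contraindicated drugs or alternative treatments during the trial are taken out: "they will be withdrawn from the study and the reason for withdrawal should be recorded". It excepts a necessary one-time administration. The opening of section 14 is permissive and says that a subject may be withdrawn.

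**What safety is meant to cover.** The safety set in 13.2.2 is every consenting woman treated with the device. Section 13.3.4 sets the horizon: "All the above safety variable data collected up to 3 months after the procedure are presented".

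**What continues after a woman leaves.** Under 15.6.3, further information on a serious event is reported periodically until it resolves or the woman is lost to follow-up. Under 16.6, a woman who drops out because of an adverse event gets care: "the subject will receive adequate treatment until recovery by taking appropriate medical measures". Section 16.6 says nothing about collecting or analysing data from that care.

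**The concern.** The device is applied on one day. A woman who leaves the study at Month 1 has had the whole exposure, and any late effect can still occur. Leaving the trial therefore gives no reason to stop counting her adverse events. Read as written, however, the protocol stops at dropout while keeping her in the denominator of a 3-month safety summary.

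The loss is also unlikely to be random. Starting another treatment, a serious reaction that rules out continuing, and an inadequate procedure are all reasons that may accompany harm or treatment failure. Take a woman with heavier vaginal bleeding, which 15.5.1 lists as an expected event. If she is put on continuing hormones, which are on the contraindicated list, she must be withdrawn under 11.6.3. Her bleeding up to that date is counted. A worsening to a higher grade, or a new event in Month 2, has no stated route into the tables.

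At stake is the safety description of a single-arm trial run for regulatory approval, where no comparator would reveal under-counting. An SAP could not repair this, because it cannot analyse data that the protocol does not provide for collecting.

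**Working it through.** **1. The sections side by side**

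| Question | Section | Answer in the protocol |
| --- | --- | --- |
| Who is in the denominator? | 13.2.2 | All treated women, dropouts included |
| How far does safety reporting run? | 13.3.4 | To 3 months |
| Which data does a dropout contribute? | 14.4 | Those collected up to dropout |
| Are adverse events sought at Visits 3 and 4 after dropout? | none | Not provided for |
| Is a reported serious event followed on? | 15.6.3 | Yes, to resolution or loss to follow-up |
| Does that later information enter the safety tables? | none | Not stated |
| Are new or non-serious events after dropout captured? | none | Not provided for |

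Section 14.3, on discontinuation of the trial, does call for follow-up. Section 14.4 has no matching line.

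**2. How many women the plan allows for.** Section 11.4 gives 72 subjects and a 10% dropout rate. 72 / (1 − 0.10) = 80, as stated, so the allowance is 80 − 72 = 8 women.

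**3. Share of the safety window that could go unobserved.** Planned observation is 80 × 3 = 240 woman-months. Assume that all 8 were treated.
- All leave at Month 1: 8 × 2 = 16, and 16 / 240 = 6.7%.
- All leave just after the procedure: 8 × 3 = 24, and 24 / 240 = 10%.
- If only 4 of the 8 were treated women, the same sums give 8 / 240 = 3.3% and 12 / 240 = 5%.

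**4. Effect on a late-event rate (assumed risks).** The documents give no adverse event rate. Suppose a 5% late-event risk in the 72 completers, and that the 8 dropouts leave before any late event. The recorded rate is 72 × 0.05 / 80 = 3.6 / 80 = 4.5%, whatever happens to the dropouts.

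| Assumed risk in the 8 | Expected women with late events | True rate | Recorded rate | Share missed |
| --- | --- | --- | --- | --- |
| 5% | 3.6 + 0.4 = 4.0 | 5.0% | 4.5% | 10% |
| 10% | 3.6 + 0.8 = 4.4 | 5.5% | 4.5% | 18% |
| 25% | 3.6 + 2.0 = 5.6 | 7.0% | 4.5% | 36% |
| 50% | 3.6 + 4.0 = 7.6 | 9.5% | 4.5% | 53% |

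The chance of at least one unseen event among the 8 is 1 − (1 − p)^8, which is 34% at p = 0.05 and 57% at p = 0.10.

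**5. Effect on an upper limit when no event is seen.** The exact one-sided 95% limit for 0 of n is 1 − 0.05^(1/n). For 0/80 it is 3.7%, and for the 72 fully followed women 4.1%. Had one unseen event been counted, 1/80 would give 5.8%.

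**The case against.** Much can be said in the protocol's defence.

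- **14.4 is worded as inclusion.** It says which analysis uses a dropout's partial data. It does not forbid collecting later safety data or order that they be discarded. That is true, but its first item keeps only what came before dropout and no other section schedules anything after, so a site following the text would have nothing further to record.
- **A reader might infer that every woman with a serious reaction is made to drop out.** The text does not support that. The criterion in 14.2 also requires that continuing be impossible, and section 14 opens with permissive wording. Only 11.6.3 is mandatory, and it covers prohibited drugs and alternative treatments, with its one-time exception.
- **A reader might infer that 14.4 contradicts 13.2.2 and 13.3.4.** It does not. One defines who is in the set, and the other presents whatever was collected up to 3 months. They sit awkwardly with 14.4 but can be read together with it.
- **The gravest harms have some protection.** Section 15.6.3 requires serious events to be reported whatever their relation to the device, and to be followed to resolution. The course of a serious event that led to dropout should therefore reach the sponsor. One could stretch the trial-period wording there to cover a new serious event in a woman who has left, but no contact is planned at which it would be found.
- **The figure of 8 is a sample-size allowance.** It may include women never treated, who are outside the safety set, and women who refuse all further contact. Some criteria, such as non-compliance, have no evident link to harm. Safety is descriptive, so no decision threshold turns on 0/80 against 1/80.

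These points narrow the concern. They leave untouched the absence of planned follow-up after dropout and the silence on tabulating what 15.6.3 and 16.6 yield.

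**Conclusion.** The point holds as a gap in safety follow-up. Followed as written, the protocol can lose new or non-serious late events in treated women who leave, and it does not say whether later information on serious events already reported is analysed. Because some reasons for leaving are plausibly linked to harm or failure, any bias in the 3-month rates is likely to be downward.

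Its size cannot be fixed from the documents. The ceiling of 6.7% to 10% of woman-months assumes that all 8 allowed dropouts were treated and left between the procedure and Month 1. Fewer treated dropouts or later departure gives less. The late-event rates and the 34% to 57% rest wholly on assumed risks. It would be tempting to say that these women are the ones most likely to have late events. That is a reasonable suspicion from the dropout reasons, but no figure in the protocol shows it.

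**What to change.** Keep the present sentence in 14.4 (2), because it also settles how dropouts' data are treated for efficacy and replacing it would disturb that clause. Add after it:

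> Treated subjects who drop out or are withdrawn continue adverse event follow-up at the Visit 3 and Visit 4 time points (by telephone if needed) unless they withdraw consent to follow-up; all safety data through Month 3, including information obtained under 15.6.3 and 16.6 after dropout, are included in the safety analysis.

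Then reconcile 11.6.3, 13.3.4, 14.2, 14.4 and 15.6.3 with that sentence, so that leaving the efficacy assessment is kept apart from ending safety observation. No treatment or withdrawal rule needs to change, and the sample size is unaffected.

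The cost is a wording amendment and up to two contacts, at time points already scheduled, for about 8 women on the plan's own allowance. The downside is some coordinator time and possibly incomplete data from reluctant subjects.

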**11.4. Calculation of Sample Size and Rationale**

According to the results of a study by Zhou et al. (2011)3 evaluating the efficacy of US-guided HIFU for the treatment of adenomyosis, 62 people out of a total of 69 subjects experienced relief of dysmenorrhea after treatment, showing a 90% improvement success rate. Based on these results, the reference success rate was assumed as 90% in this clinical trial to calculate the number of subjects required to satisfy the hypothesis that the success rate of the ‘ALPIUS device will be non-inferior when compared to the reference success rate’.

ALPINION Medical Systems Co., Ltd. 18/45

[figure not shown]

[figure not shown]

Protocol No. APM-03 Version 1.10/Date 20180103

[figure not shown]

In addition, in the results of a recent study evaluating the efficacy of the US-guided HIFU procedure for adenomyosis, Zhang et al. (2014)5 evaluated the degree of relief of menorrhagia and dysmenorrhea and showed a success rate of 79.5% to 87.9% while Wang et al. (2009)12 suggested an improvement success rate of 66.7%; thus, we assumed that 77.7%, which is greater than the minimum value of 66.7%, would be the ‘minimum success rate that satisfies non-inferiority’ in this study (i.e. non-inferiority threshold = 77.7%-90% = -12.3%).

The statistical hypothesis of this study is as follows.

H0: PA - P0 ≤ - δ vs H1: PA - P0 > - δ

- - PA: Expected success rate of the investigational medical device
  - P0: Reference success rate
  - δ (>0): Non-inferiority threshold

To calculate the number of samples for hypothesis testing, the number of subjects satisfying the non-inferiority hypothesis was calculated as follows through PASS13 (NCSS statistics software, Kaysville, UT) based on the following assumptions: significance level of 0.025, power of 80%, reference success rate and expected success rate of this device are set at 90%, non-inferiority limit of 12.3%, the difference between the actual success rate and the reference success rate as D=0.

[figure not shown]

As a result, a total of 72 subjects were calculated, and 80 subjects were enrolled in consideration of the dropout rate of 10%.

<Reference for Calculation of Number of Subjects>

1. X Zhang et al. Effective ablation therapy of adenomyosis with ultrasound-guided high-intensity focused ultrasound. International Journal of Gynecology and Obstetrics. 2014;124:207-211.

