**13.2.1. Efficacy Analysis Set**

- FAS (Full Analysis Set): As the main analysis set for the assessment of efficacy in this study, it is defined as any subject who participates in the study after consenting to participation, receives the application of investigational medical device, and has at least one valid evaluable data.

ALPINION Medical Systems Co., Ltd. 30/45

[figure not shown]

Protocol No. APM-03 Version 1.10/Date 20180103

- PP analysis set (Per Protocol Analysis Set): It is defined as all subjects who participated in the study after consenting to participate in the study, received the investigational medical device, and completed the clinical study according to the study plan without serious protocol violations until the end of the study. Those who received drugs or alternative treatments that affect efficacy during the clinical trial period are excluded from the PP analysis set.

1. *Major protocol violations to be excluded from the analysis set*
2. Those who received drugs or alternative treatments that affect efficacy during the clinical trial period

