**13.2.3. Handling Missing Data (missing values)**

If a missing value occurs in the efficacy endpoints, the variable is excluded from the analysis.

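### Sections 14.3 and 14.4 drop every withdrawn woman from efficacy, against the FAS definition, and no rule counts a treated woman who leaves as not improved, so the primary success rate can be biased upward

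*Protocol*

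**What the plan says.** Protocol 13.2 makes the FAS the main set for efficacy and the PP set auxiliary. Section 13.2.1 puts a consenting woman in the FAS if she "receives the application of investigational medical device, and has at least one valid evaluable data". Completion is required only for the PP set. Women who took drugs or alternative treatments affecting efficacy are likewise removed only from the PP set.

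Sections 14.3 and 14.4 set a different rule. In 14.3: "All discontinued subjects will be included in the safety analysis and will be excluded from the efficacy assessment". In 14.4, data collected up to a subject's "dropout will be included in the safety analysis and will be excluded from the efficacy assessment". Neither sentence is limited to the PP set.

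The dropout criteria in 14.2 include "In case of concomitant use of surgery, drug, or medical device that may affect safety and efficacy assessment", a serious adverse reaction that prevents continuation, and "If treatment is not performed properly". Section 11.6.3 adds: "If any of the above contraindicated drugs or alternative treatments were received during the clinical trial period, they will be withdrawn from the study". It makes an exception, at the investigator's discretion, for a necessary one-time administration unrelated to the study.

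On missing data, 13.2.3 says: "If a missing value occurs in the efficacy endpoints, the variable is excluded from the analysis".

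The primary test in 13.3.2 passes if the lower limit of the one-sided 97.5% confidence interval for the Month-3 improvement rate exceeds 0.777.

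**The concern.** There are two linked problems.

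The first is a contradiction about who belongs in the efficacy analysis. A treated woman with one evaluable value who later leaves is in the FAS under 13.2.1 and outside efficacy under 14.4.

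The second is selection. Whether 14.3, 14.4 or 13.2.3 does the removing, a treated woman who leaves disappears from both the numerator and the denominator of the Month-3 rate. If women leave more often because the procedure did not help, the rate among those who remain overstates the rate among those treated.

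The trial has one arm and one pass/fail test, so no control group shares the distortion. Raising 72 to 80 for 10% dropout restores precision but does nothing about bias.

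**Working it through.** **Inputs.** From 11.4: one-sided alpha 0.025, power 80%, reference and expected rate 90%, margin 12.3 points (threshold 0.777), 72 evaluable, 80 enrolled at 10% dropout. From 13.3.2: the pass rule. Assumptions: all 80 enrolled are treated, and the limit is exact (Clopper-Pearson), because 13.3.2 names no interval method.

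**The plan's own figure.** A one-sample score test of 0.777 against 0.90 (variance at 0.777), with exact binomial enumeration, first reaches 80% power at n = 72: reject at 63 or more, power 0.820, actual alpha 0.026. The exact test first reaches 80% at n = 73 (power 0.809). Then 72 / 0.90 = 80. The sample size reproduces.

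**How a withdrawn woman is counted.**

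| Treated woman | 13.2.1 | 14.3 / 14.4 | 13.2.3 | In the Month-3 rate? |
|---|---|---|---|---|
| Month-1 rating, leaves in month 2 | in FAS | out | Month-3 value missing | no, under either rule |
| Month-3 rating, classed as a dropout | in FAS | out | not missing | depends on which section governs |
| Leaves before any evaluable value | not in FAS | out | missing | no |

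No row counts her as not improved.

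**Pass marks.** The pass mark c(n) is the smallest x with P(Bin(n, 0.777) ≥ x) ≤ 0.025.

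- n = 72: c = 64. 64/72 = 88.9%, lower limit 0.793, pass.
- n = 80: c = 70. 70/80 = 87.5%, lower limit 0.782, pass.
- The same 64 successes over 80 treated: 64/80 = 80.0%, lower limit 0.696, fail.

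The last line is the extreme case, in which all eight women removed are counted as failures.

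**False-pass risk.** Let the true rate among all treated be 0.777. Each woman is removed with probability d, and a share f of those removed are failures. The success rate among those kept is

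p_kept = [0.777 − d(1 − f)] / (1 − d).

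For d = 0.10 and f = 0.50: (0.777 − 0.05) / 0.90 = 0.808.

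With M ~ Bin(80, d) removed, the chance of passing is

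Σ over m of P(M = m) × P(Bin(80 − m, p_kept) ≥ c(80 − m)).

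| Share of removed who are failures | 10% removed: p_kept | false pass | 5% removed: p_kept | false pass |
|---|---|---|---|---|
| 25% | 78.0% | 2.0% | 77.8% | 1.7% |
| 50% | 80.8% | 6.5% | 79.2% | 3.2% |
| 75% | 83.6% | 17.9% | 80.5% | 5.7% |
| 100% | 86.3% | 39% | 81.8% | 9.7% |

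With nobody removed the risk is 1.9%. If 10% are removed for reasons unrelated to outcome (22.3% of them failures), it is 1.7%. The excess comes only from outcome-related removal.

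**Size of the bias.** Take 90% success in completers and 10% removed. If 0%, 25%, 50% or 75% of those removed would have been successes, the all-treated rate is 0.81 + 0.10 × that share = 81.0%, 83.5%, 86.0% or 88.5%. The reported 90% is then too high by 9.0, 6.5, 4.0 or 1.5 points.

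**The case against.** The strongest reply is that the contradiction and the bias are largely separate. A reader might infer that the FAS rule and section 14.4 give two different primary results, using the woman who leaves in month 2. They do not for her: she has no Month-3 rating, so 13.2.3 removes her from the primary analysis either way. The conflict changes the primary rate only for women who have a Month-3 rating and are classed as dropped out or discontinued. It does affect her Month-1 result, which is a secondary endpoint. This objection stands. It also means that deleting the exclusions in section 14 would not by itself remove the bias.

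A reader might also call the withdrawals device failures. The documents do not support that. The criterion on other surgery, drugs or devices is broad, and the contraindicated list includes corticosteroids and oral contraceptives, which may be taken for unrelated reasons. It names no analgesics, so persistent pain alone does not trigger withdrawal. A procedure not performed properly may mean the device was never applied. Consent withdrawal, non-compliance and unrelated death need not be failures. Lack of benefit is a plausible reason under some criteria, not an established one.

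A third inference is that the 90% reference is an all-treated rate and so not comparable with a completers' rate. Section 11.4 says only that "62 people out of a total of 69 subjects experienced relief of dysmenorrhea after treatment". It does not say whether the 69 were all those treated or those followed up, so nothing here rests on that comparison.

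Finally, the 39% figure is a worst case: the whole 10% allowance would have to consist of failures.

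**Conclusion.** The point holds. Sections 14.3 and 14.4 contradict the FAS, and together with 13.2.3 they leave the only confirmatory test without a rule that counts a treated woman who leaves as not improved. Upward bias is an inference: it requires that women who leave do worse than those who stay.

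Under the stated assumptions the false-pass risk at 10% removed stays below the nominal 2.5% if a quarter of those removed are failures, is about two and a half times nominal if half are, and reaches 39% only if all are. At 5% removed it runs from 1.7% to 9.7%. The actual number and reasons of withdrawals are not in the document, so no single figure can be given. The wording needs correcting before the data are analysed, because it decides who is counted in the pass/fail test.

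**What to change.** 1. In the third item of 14.3 and the second item of 14.4, delete the exclusion from efficacy or limit it to the PP set, so that 13.2.1 governs.
2. Amend 13.2.1 so that every woman in whom the device was applied is in the primary denominator. Replace 13.2.3 for the primary endpoint: a treated woman who has no Month-3 rating, or who received another adenomyosis treatment before it, counts as not improved. Add sensitivity analyses on observed cases and with imputation from the Month-1 relief score. Do not apply the not-improved rule to a trial-level stop under 14.1, where relieved women would be scored as failures for an unrelated reason.
3. State that Month-1 and Month-3 scores and adverse events are still collected from withdrawn women who agree. Keep the PP exclusions as they are.

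**Cost.** This is a change of wording plus continued data collection. The observed rate may fall. If 90% holds among all treated women, exact power with 80 in the denominator is 82.7% (pass mark 70/80), so the planned size suffices. If 90% holds only among completers, power is lower. In the extreme case where 10% leave and all count as not improved, the all-treated rate is 0.90 × 0.90 = 81% and power is about 8.6%. The sponsor should therefore state which population the 90% refers to.
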